#### Evaluation of adherence to intervention

Descriptive statistics will be used to evaluate adherence to the two interventions, overall and by general practice location, participant sex, and age. Counts and proportions will be used for the binary measures by each Intervention. For Intervention 2, of individuals who opened the bundle at least once, the number of times a weblink in the SMS bundle is clicked on, the number of times each of the two videos are viewed, and webpage viewed will be presented as total counts, and rates per individual, respectively.

#### Economic evaluation

Led by JBL, the economic evaluation will be conducted using an existing calibrated and validated microsimulation platform, Policy1-Bowel, developed by the Daffodil Centre [7, 23] The model has been used to evaluate the health benefits, burden and harms, and cost-effectiveness of different bowel cancer screening approaches to inform the bowel cancer screening policy in Australia [7, 23]. In brief, the model simulates the life histories of bowel lesion(s) (conventional adenoma and sessile serrated lesion) and cancer development, bowel cancer survival, and bowel cancer screening in individuals in Australian population. Each simulated individual could develop up to ten adenomas and ten serrated lesions simultaneously. The simulated individuals who have advanced adenoma(s) (i.e. a conventional adenoma that is large, with high-grade dysplasia, or with villous histology) and/or sessile serrated lesion(s) have an annual risk of developing into a preclinical cancer. Over time, a preclinical cancer can progress to a more advanced stage or become clinically diagnosed due to symptoms or bowel cancer screening. Patients diagnosed with bowel cancer have a risk of dying, which varies by cancer stage at diagnosis and time since cancer diagnosis. In the model, patients who survive for 5 years after cancer diagnosis are assumed to no longer be affected by bowel cancer and have no additional risk of dying from bowel cancer compared with the average population with no bowel cancer.

For this economic evaluation, the NBCSP participation rates for each intervention arm in the trial and the costs associated with sending a GP practice-endorsed SMS with/without additional motivational material will be incorporated into the Policy1-Bowel model. Cost-effectiveness and the difference in the 5-, 10- and 20-year bowel cancer incidence and mortality outcomes among participants of the two SMS intervention arms versus the control arm will be estimated. Furthermore, the model will also be used to estimate the budget impact on the health care cost and the 5-, 10-, and 20-year cancer incidence and mortality reduction in the Australian population if the SMS intervention was adopted and implemented nationwide compared with the current practice.

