### Hypotheses

Our primary hypotheses are:A GP practice-endorsed SMS sent from general practice to patients aged between 49 and 60 years old and due for a NBCSP kit will increase the proportion of patients who return the NBCSP kit within 6 months of when their kit is sent compared to usual care;A SMS bundle with a GP endorsement of the NBCSP and additional material (i.e. motivational and instructional videos) from general practice to patients aged between 49 and 60 years old and due for a NBCSP kit will increase the proportion of patients who return the NBCSP kit within 6 months of when their kit is sent compared to usual care;Proportion of general practice patients who return the NBCSP kit within 6 months of when the kit was due will differ between patients aged between 49 and 60 years old and due for a NBCSP kit who receive SMS bundle with a GP endorsement of the NBCSP and additional material (i.e. motivational and instructional videos) compared to those who receive an SMS with only GP endorsement of the NBCSP.

Secondary hypotheses:

Sending a GP practice-endorsed SMS with/without additional motivational material to people before their kit is sent will be cost-effective compared with usual care.

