#### Economic evaluation outcome

The economic model-estimated cost-effectiveness of both sending a GP practice-endorsed SMS with/without additional motivational material to people before they are due to do their NBCSP kit to increase the uptake of the NBCSP and the SMS intervention compared with usual care.

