#### Sample size {14}

Sample size was based on 80% power for an overall two-sided significance level of 5% (alpha), and an intraclass correlation coefficient (ICC) of 0.01. Planned primary comparisons are the two intervention arms (SMS only and SMS bundle) with the control arm, respectively, and the SMS only intervention with the SMS bundle. The Holm-Bonferroni correction was used to control the family-wise error rate across three pairwise comparisons. Thus, for the purposes of the sample size calculations, we conservatively set the alpha at 0.017. We assumed that 34% of patients in the control arm will have completed their FIT, based on the National screening data [20]. Sixty-three practices with an average of 260 of eligible patients per practice (standard deviation = 197; range 51 to 753; coefficient of variation = 0.76) [15] will be sufficient to detect a difference of 10% absolute increase in participation in the NBCSP within 6 months from when the NBCSP kit is due between each intervention arm (SMS only and SMS bundle) and control arm (44% vs 34%), respectively; and to detect a smaller difference of 7.5% (44% vs 51.5%) between the SMS only and SMS bundle intervention arms. The total of 63 practices allows for an additional practice per arm for potential loss of practices due to closures or merges. A national 10% increase in screening participation would prevent 27,000 bowel cancers and 16,800 deaths and is associated with an additional $200 million in costs over current screening levels over the next 20 years [4]. We anticipate that adding the weblinks to motivational and instructional videos in the SMS would have a smaller additional effect on increasing screening participation compared to a SMS only.

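### The economic evaluation prespecifies each SMS strategy against usual care only and leaves out SMS bundle versus SMS only, the contrast that would show which to adopt

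*Protocol article*

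**What the plan says.** Every economic statement in the protocol uses the same reference point.

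- **Objectives {7}:** the economic aim sets the two interventions against usual care.
- **Hypotheses:** the secondary hypothesis is that an SMS, with or without the extra material, "will be cost-effective compared with usual care".
- **Economic evaluation outcome:** the sentence is hard to parse, but it ends "and the SMS intervention compared with usual care", and usual care is the only comparator it names.
- **Economic evaluation:** incidence and "mortality outcomes among participants of the two SMS intervention arms versus the control arm will be estimated". The national budget impact is to be modelled "if the SMS intervention was adopted and implemented nationwide compared with the current practice". This is in the singular, and the section does not say whether it means SMS only, the bundle, or both.

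The same section says that the model takes in "the NBCSP participation rates for each intervention arm in the trial and the costs associated with sending a GP practice-endorsed SMS", with and without the motivational material.

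On effectiveness, the protocol plans all three pairs. Sample size {14} lists each SMS arm against control "and the SMS only intervention with the SMS bundle", and Outcomes {12} and Statistical methods {20a} repeat the three comparisons. Sample size {14} also says: "We anticipate that adding the weblinks to motivational and instructional videos in the SMS would have a smaller additional effect".

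**The concern.** Usual care, SMS only and SMS bundle are three alternatives, and a practice or a national programme would adopt one of them. Once a plain SMS is an option, the question for the bundle is what the videos add and at what extra cost. A ratio of the bundle against usual care does not answer that. It averages the gain from the message itself with the gain from the videos, and can make the videos look like good value when the message has done most of the work. The reverse is also possible: if the videos are nearly free and effective, the ratio against usual care understates their value.

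At stake is the policy conclusion. Both strategies could pass as cost-effective against usual care, and the secondary hypothesis could be declared met for both, without the planned economic results showing which one to implement. The Introduction says that the earlier trial could not separate the message from the linked material. The present trial resolves this for effectiveness, but its economic plan does not carry the separation through.

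**Working it through.** **1. How much weight the design gives to bundle versus SMS only**

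Inputs from Sample size {14}: 80% power, ICC 0.01, alpha 0.017 per comparison, mean 260 patients per practice, coefficient of variation 0.76, 44% versus 51.5% for SMS only versus bundle, 34% versus 44% for an SMS arm versus control, and one spare practice per arm.

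- Design effect = 1 + ((1 + 0.76²) × 260 − 1) × 0.01 = 5.09.
- Bundle versus SMS only: 924 patients per arm before inflation, and 924 × 5.09 / 260 = 18.1 practices per arm by the normal approximation.
- With a t reference on 2(k − 1) degrees of freedom, power is 78.7% with k = 19 practices per arm, 81.3% with 20 and 83.5% with 21. Twenty plus one spare gives 21 × 3 = 63, the protocol's figure. (The normal approximation gives 84.4% with 20.)
- SMS arm versus control: 495 patients per arm before inflation, or 9.7 practices. Power with 20 practices per arm is about 98 to 99%.

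The stated sample size is reproduced. The bundle versus SMS-only contrast is the demanding one and sets the number of practices.

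**2. What the choice of comparator does to the ratio**

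The protocol gives no costs, so these are assumptions: SMS only costs c per patient, the bundle costs r × c, and only messaging costs are counted. From the protocol, SMS only adds 10 points (44% − 34%). Let the bundle add a further d.

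- Bundle versus usual care: r × c / (0.10 + d) per extra returned kit.
- Bundle versus SMS only: (r − 1) × c / d per extra returned kit.
- SMS only versus usual care: c / 0.10 = 10c.

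With r = 2:

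| Added gain d | Bundle v usual care | Bundle v SMS only |
|---|---|---|
| 7.5 points (planned) | 2c/0.175 = 11.4c | c/0.075 = 13.3c |
| 3 points | 2c/0.13 = 15.4c | c/0.03 = 33.3c |
| 1 point | 2c/0.11 = 18.2c | c/0.01 = 100c |
| 0 points | 2c/0.10 = 20c | dominated |

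Over these rows the ratio against usual care less than doubles, while the ratio against SMS only goes from similar to dominated.

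**3. Range over the unknown cost ratio** (first figure against usual care, second against SMS only)

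| r | d = 7.5 points | d = 3 points | d = 1 point |
|---|---|---|---|
| 1.1 | 6.3c; 1.3c | 8.5c; 3.3c | 10c; 10c |
| 1.5 | 8.6c; 6.7c | 11.5c; 16.7c | 13.6c; 50c |
| 2 | 11.4c; 13.3c | 15.4c; 33.3c | 18.2c; 100c |
| 3 | 17.1c; 26.7c | 23.1c; 66.7c | 27.3c; 200c |

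The two ratios are equal when (r − 1)(0.10 + d) = r × d, that is, when d = 0.10 × (r − 1). At the planned 7.5 points this is r = 1.75. Above that cost ratio the comparison with usual care flatters the bundle; below it, it understates the bundle's value.

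**The case against.** The strongest reply is that nothing is lost. Participation by arm and the costs with and without the videos enter one model, so the bundle versus SMS-only increment is the difference between two planned results. The article is also a condensed account: it gives no threshold, discount rate or uncertainty method for the model, and a fuller plan may hold the incremental analysis. If the videos added only one point, the primary effectiveness comparison, reported with its confidence interval, would show that openly. Finally, the size of the problem rests on costs that the protocol does not give, and cost per returned kit is not what a microsimulation with health-care costs, incidence and mortality will report.

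Much of this stands. A reader might infer that the evaluation is unable to show whether the bundle is worth its extra cost. The documents do not support that, because the increment can be derived from planned outputs. Nor do the ratios above carry over to the model's results; they show only how the choice of comparator works.

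What does not stand is the claim that the comparator is merely a detail left out. The aim, the hypothesis and the methods each name it, and each names usual care or the control arm. That is a stated choice. An increment worked out after the results are known is left to discretion, and an effectiveness interval does not by itself say whether a small gain is worth its cost.

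**Conclusion.** The point holds as a gap in prespecification. The economic plan compares each SMS strategy with usual care only, although bundle versus SMS only is a primary effectiveness contrast and the one that sets the number of practices.

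The size depends on costs that are not in the protocol. If the bundle costs twice the plain SMS, the two ratios at the planned 7.5 points are 11.4c and 13.3c, about 17% apart (13.3/11.4 = 1.17). They separate widely only if the videos add little: 18.2c against 100c at one point. A reader might take that last pair, a 5.5-fold difference, as the expected distortion. The documents do not support this, since it needs both an assumed doubling of cost and a gain far below the planned one. If the bundle's extra cost is trivial, the matter has little practical effect. This is a nearly free improvement to the economic plan and does not affect the trial's effectiveness results.

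**What to change.** In Objectives {7}, Economic evaluation outcome and Economic evaluation, prespecify a fully incremental analysis of the three strategies. Order them by cost, remove dominated options, and report SMS only versus usual care and bundle versus SMS only, with the trial's uncertainty in those differences carried through the model. Reword the economic outcome so that its comparisons can be read unambiguously. State whether the national budget impact covers SMS only, the bundle, or each separately.

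The cost is a change of wording and one extra comparison to report. No new data are needed, the inputs for all three strategies are already planned, and the sample size is unchanged.

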### Plans to give access to the full protocol, participant-level data, and statistical code {31c}

To assist with reproducible research, the full protocol, non-identifiable participant-level data, and statistical code will be made available to external researchers upon reasonable request. The steering committee will manage external requests for these materials.

### Composition of the data monitoring committee, its role and reporting structure {21a}

JT, PC, JM, AW, TJ, JE, SF, and MJ will report to the investigators as to the data collection and analysis plan.

### Adverse event reporting and harms {22}

Any adverse events and other unintended effects that may arise from the trial intervention will be reported to the University of Melbourne Office of Research Ethics and Integrity Ethics Committee (OREI).

### Frequency and plans for auditing trial conduct {23}

Progress reports will be submitted annually to the University of Melbourne Office of Research Ethics and Integrity (OREI) and regularly to the Australian and New Zealand Clinical Trials Registry (ANZCTR). This will be completed by the Project Lead JM. Progress will be reported to the investigators with quarterly meetings.

### Plans for communicating important protocol amendments to relevant parties (e.g. trial participants, ethical committees) {25}

Any amendments to the protocol will be discussed in the weekly meetings with the SMARTERscreen steering group and project officers (JM, JE, PC, BG, JT, LB, SF, and MJ) and protocol amendments will be communicated to the investigators by email and at quarterly meetings. The project officers will communicate with the rest of the steering committee to ensure they are all involved in the decision-making. They will also inform the ethics committee (OREI) and the trial register (ANZCTR) with modifications to the protocol or progress of the trial as necessary.

## Dissemination plans {31a}

SPIRIT guidance: Plans for investigators and sponsor to communicate trial results to participants, healthcare professionals, the public, and other relevant groups (e.g. via publication, reporting in results databases, or other data sharing arrangements), including any publication restrictions.

## Discussion

This protocol describes the trial design informed by the SMARTscreen trial which demonstrated that using an SMS with a combination of additional features including endorsement by a primary care clinician, a motivational video, instructions for how to do the NBCSP kit, and links to extra information was efficacious for increasing bowel cancer screening [15]. This trial—‘SMARTERscreen’—will address the limitations we found in SMARTscreen which included a potential lack of generalisability as we only included regional practices from one state in Australia, the use of incomplete data as the data used to calculate the results were from general practice electronic health records, and we only had aggregated data at the practice level.

Increasing participation in the Australian NBCSP has the potential to reduce bowel cancer incidence and reduce associated health costs over 20 years [7] and bring the Australian screening programme in line with international bowel cancer screening programmes which have much higher participation rates of 60–70% [24]. This is one of the health priorities of the Australian Government.

## Conclusion

This trial will build on previous research conducted by this research group and has the potential to demonstrate the effectiveness of a simple technological intervention to improve screening uptake which is scalable and sustainable.

## Trial status

The SMARTERscreen trial has approval from the Human Research Ethics Committee at the University of Melbourne and started recruitment on 12 February 2023. Protocol is dated 7 June 2023; version 1.0.

All practices have been recruited (21 July 2023) and we anticipate data extraction from the NCSR will begin in September 2023. The intervention period will begin once recruitment and baseline data have been collected. The intervention will begin in early 2024 once individuals’ eligibility is determined and randomisation is implemented.

## Data Availability

The trial data set will be available to the trial coordinator and the statistician. These data including the statistical code will not be available for public access.

## Abbreviations

ANZCTR: Australia New Zealand Clinical Trial Registry
CRC: Colorectal Cancer
EHR: Electronic Health Record (i.e. general practice patient record)
FIT: Immunochemical Faecal Occult Blood Test
GP: General Practitioner
HPP: Health Provider Portal
ITT: Intention To Treat analysis
NBCSP: National Bowel Cancer Screening Program
NCSR: National Cancer Screening Register
PRODA: Provider Digital Access
RCT: Randomised Controlled Trial
SAP: Statistical Analysis Plan
SMS: Short Messaging Service
